### Calculated capecitabine dose at dose level 50%

| 50% dose level
(twice daily) |                | Number of tablets
in the morning |       | Number of tablets
in the evening |       |
|---------------------------------|----------------|-------------------------------------|-------|-------------------------------------|-------|
| BSA                             | Dose per admin | 150mg                               | 500mg | 150mg                               | 500mg |
| ≤ 1.38                          | 450mg          | 3                                   | -     | 3                                   | -     |
| 1.39 – 1.52                     | 500mg          | -                                   | 1     | -                                   | 1     |
| 1.53 – 1.78                     | 500mg          | -                                   | 1     | -                                   | 1     |
| 1.79- 1.92                      | 600mg          | 4                                   | -     | 4                                   | -     |
| 1.93 – 2.18                     | 650mg          | 1                                   | 1     | 1                                   | 1     |
| ≥ 2.19                          | 650mg          | 1                                   | 1     | 1                                   | 1     |
|                                 |                |                                     |       |                                     |       |

### 5FU

For patients unable to receive capecitabine, 5FU will be administered as protracted venous infusion via a central line at 200mg/m^2/day. Administration and anticoagulation will be according to local treatment policy.

### 8.2.2 Cetuximab

**There are no known interactions between cetuximab and the cytotoxic agents being used. The latter should therefore be administered according to the schedule and precautions described above. The following advice applies just to the additional use of cetuximab.**

#### Pre-treatment

Prior to the first infusion, patients on the cetuximab research arm of the study (Arm B) must receive pre-medication with an appropriate antihistamine. The antihistamine (to reduce the risk of an allergic reaction) should be administered prior to the starting dose and the subsequent weekly doses.

Cetuximab (ErbixTM) 400mg/m^2 (initial) dose shall be given as an IV infusion over 120 minutes. Subsequent weekly doses of 250mg/m^2 shall be given as an infusion over 60 minutes. The maximum infusion rate must not exceed 10 mg/min cetuximab (ErbixTM) (corresponding to 2 mL/min ready-to-use solution).

Close monitoring of the patient is required during the infusion and for at least 1 hour after the end of the infusion. Resuscitation equipment must be available. The supervising clinician should be in the room or unit during the first dose of cetuximab.

On days where patients are receiving radiotherapy, cetuximab should be given prior to radiotherapy.

Cetuximab is contraindicated in patients with known severe (grade 3 or 4) hypersensitivity reactions to cetuximab. There are no specific drug interactions documented with cetuximab, however, any agent that could interfere with a patient's immune system should be avoided. Exceptions to this include the study regime and necessary supportive treatments (including anti-emetics, corticosteroids etc).

#### Dosage and Administration Procedure:

##### Initial dose:

The total **initial dose** (first infusion) is **400 mg/m^2 (80 mL/m^2 ready-to-use solution)** and is administered over a period of 120 minutes (maximum infusion rate of 10 mg/min, corresponding to 2 mL/min ready-to-use solution). Patients must be pre-treated with an antihistamine. Observe the patient during infusion and for one hour afterwards. Check the vital signs pre-, mid-, post- and one hour post-infusion. Use a sterile 0.9% NaCl solution to flush the line at the end of infusion.

##### Further infusions:

The **weekly dose** (all further infusions) is **250 mg/m^2 (= 50 mL/m^2 ready-to-use solution)** and is administered over a period of 60 minutes (maximum infusion rate of 10 mg/min, corresponding to 2 mL/min ready-to-use solution). It is recommended that the patient is pre-treated with an antihistamine prior to each infusion. Observe the patient during infusion and for one hour afterwards. Check the vital signs pre-, mid-, post- and one hour post-infusion. Use a sterile 0.9% NaCl solution to flush the line at the end of infusion.

**Do not mix cetuximab solution with any intravenously administered medicinal product other than a sterile 0.9 % NaCl solution.** Use a separate infusion line for cetuximab infusion. For dose reduction due to adverse events, see the section 8.4.2. **Wait at least one hour after completing the cetuximab infusion before patient receives chemotherapy.**

### **Preparation and Administration of the Infusion**

Cetuximab solution contains no antimicrobial preservative or bacteriostatic agent. This means care must be taken to ensure aseptic handling when preparing the infusion.

There are two options:

#### **Syringe Pump:**

- Calculate the required amount of cetuximab per patient and administration (e.g., 250 mg/m^2 for a 2 m^2 patient = 500 mg cetuximab). Calculate the required amount in volume cetuximab solution at 5 mg/mL (e.g., 500 mg cetuximab = 100 mL cetuximab 5 mg/mL)
- Draw up the volume calculated above from one or several cetuximab 5 mg/mL vials, using one or several appropriate sterile syringes attached to a suitable needle.
- Remove the needle, affix the infusion line to the first filled syringe, and prime it with cetuximab.
- Put the first filled syringe into the syringe pump and set the rate. Repeat for remaining syringes.
- Monitor the infusion rate. The calculated infusion rate must not exceed the maximum infusion rate of 10 mg/min, i.e. 120 mL/h of the ready-to-use solution.
- Use a sterile 0.9% NaCl solution to flush the line at the end of infusion.

#### **Infusion Pump or Gravity Drip:**

- Calculate the required amount of cetuximab per patient and administration (e.g., 250 mg/m^2 for a 2 m^2 patient = 500 mg cetuximab). Calculate the required amount in volume cetuximab solution at 5 mg/mL (e.g., 500 mg cetuximab = 100 mL cetuximab 5 mg/mL)
- Take an infusion bag of adequate size (e.g., 250 mL) of 0.9% NaCl solution for infusion (isotonic saline for infusion).
- Draw up the volume calculated above from the NaCl bag, using an appropriate sterile syringe attached to a suitable needle. Discard the drawn up NaCl solution.
- Draw up the volume calculated above from one or several cetuximab 5 mg/mL vials, using one or several appropriate sterile syringes attached to a suitable needle.
- Fill the calculated volume of cetuximab into the NaCl infusion bag.
- Affix the infusion line and prime it with cetuximab before starting the infusion.
- Monitor the infusion rate. The calculated infusion rate must not exceed the maximum infusion rate of 10 mg/min.

- Use a sterile 0.9% NaCl solution to flush the line at the end of infusion.

A one-hour observation period is recommended after the cetuximab infusion.

For the initial dose, the recommended infusion period is 120 minutes. For subsequent weekly doses, the recommended infusion period is 60 minutes.

The maximum infusion rate must not exceed 10 mg/min (i.e., 2 mL/min of the 5 mg/mL solution, or, after dilution of 1 part cetuximab 5 mg/mL in 4 parts 0.9%-NaCl solution (1:5 dilution) 10 mL/min = 600 mL/h).

### **Recommended materials, compatibility and stability**

Infusion sets or syringes made of polyethylene, polyurethane, polyolefine thermoplastic, polyamide glass microfibre, polypropylene and polyvinyl chloride have been tested for compatibility with cetuximab, and are recommended for use.

Cetuximab is stable, and is compatible with infusion systems made from any combination of the recommended infusion system components when administered at room temperature (up to 25°C). Preparations of cetuximab in the recommended infusion containers are chemically and physically stable for up to 48 hours at controlled room temperatures up to 25 °C. The product contains no antimicrobial agent and should be used immediately. If not used immediately, in-use storage times and conditions prior to use are the responsibility of the user. In-use storage at 2-8 °C should not exceed 24 hours, unless preparation has taken place under controlled and validated aseptic conditions. Discard any unused portion of the vial.

## 8.3 Possible side Effects

### 8.3.1 Cisplatin and Capecitabine (or 5FU)

**Haematological toxicity:** Myelosuppression is uncommonly observed with cisplatin and capecitabine (or 5FU). Neutropaenia and thrombocytopaenia should be monitored according to the recommended protocol and appropriate dose modifications made. Anaemia may occur cumulatively with cisplatin and should be corrected during radiotherapy to maintain the haemoglobin > 12g/dL.

**Nephrotoxicity:** Renal toxicity has been noted in about one third of patients given a single dose of cisplatin when prior hydration has not been employed. Renal toxicity becomes more prolonged and severe with repeated courses of the drug. Serum renal function should be used to estimate renal function as a baseline prior to and during treatment using the Cockcroft & Gault formula (Appendix II). An EDTA clearance should be performed where indicated in the protocol and an appropriate dose adjustment made to the chemotherapeutic agents.

**Gastrointestinal toxicity:** Nausea and vomiting is common following cisplatin, usually starting within 1 hour of treatment and lasting up to 24 hours. Anorexia, nausea and occasional vomiting may persist for up to one week. Nausea occurs less commonly with capecitabine (or 5FU).

Diarrhoea occurs with capecitabine (or 5FU) and patients should receive advice regarding discontinuation of therapy and use of loperamide or codeine phosphate. Clinicians should be aware of infective causes of diarrhea (e.g. *Clostridium difficile*), and patients should be tested in cases of concern. Antibiotic treatment is not recommended routinely but may be required in such circumstances. Stomatitis occurs with capecitabine and patients should receive advice regarding good oral care, and the use of mouthwash (e.g. Corsodyl™).

**Hand-foot syndrome (Palmar-plantar erythrodysaesthesia/PPE):** Occurs with capecitabine (or 5FU) and is reversible, where necessary with dose delay and reduction (see below). Other side effects include dermatitis, pigmentation and nail changes.

**Cardiac:** An infrequent association with capecitabine (or 5FU) is acute chest pain that appears to be related to coronary artery spasm and occurs more frequently in patients with known ischaemic heart disease. Fluoropyrimidines are also associated with tachyarrhythmias and ECG changes.

**Neurotoxicity:** Cisplatin neurotoxicity is characterised by peripheral neuropathies and paraesthesia in both upper and lower extremities and while reversible, may take a year or more to recover. Losses of taste and seizures have also been reported. This is quite different to 5FU associated neurotoxicity characterised by a transient reversible cerebellar syndrome.

**Ototoxicity:** Ototoxicity is cumulative with cisplatin and is not reversible. Unilateral or bilateral tinnitus, which is usually reversible, and/or hearing loss in the high frequency range, may occur. These abnormalities usually appear within 4 days after drug administration. Patients with significant neuro- and ototoxicity are not eligible and where

necessary patients should be changed to carboplatin according to the protocol (8.4 non-haematological toxicities).

**Anaphylaxis:** Reactions to cisplatin therapy have been occasionally reported in patients who were previously exposed to cisplatin. Patients who are particularly at risk are those with a prior history or family history of atopy. Serious reactions may be controlled by IV adrenaline, corticosteroids or antihistamines.

**Serum Electrolyte Disturbances:** Hypomagnesaemia, hypocalcaemia, hyponatraemia, hypokalaemia and hypophosphataemia have been reported to occur in patients treated with cisplatin and hypomagnesemia may occur with cetuximab and should be monitored according to the protocol.

**Other Toxicities:** Hair loss is not expected with this combination but may rarely occur with most chemotherapeutic agents. Vascular toxicities coincident with the use of cisplatin in combination with other antineoplastic agents have been reported rarely. These events may include myocardial infarction, cerebrovascular accident, thrombotic microangiopathy (haemolytic uraemic syndrome) or cerebral arteritis. There have been reports of optic neuritis, papilloedema and cerebral blindness following treatment with cisplatin.

### 8.3.2 Cetuximab

In approximately 5% of patients, hypersensitivity reactions may occur during treatment with cetuximab; about half of these reactions are severe.

The most commonly reported side effect with cetuximab is an acne-like skin rash, reported in approximately 80% of the patients. Less frequently skin reactions such as pruritus, dry skin, desquamation, hypertrichosis, or nail disorders (e.g. paronychia) can occur. Approximately 15% of the skin reactions are severe. The skin reactions generally resolve, without sequelae, over time following cessation of treatment if the recommended adjustments in dose regimen are followed, though occasionally may require the use of topical or even systemic antibiotics.

Mild to moderate infusion-related reactions can occur with cetuximab infusion; symptoms such as fever, chills, nausea, vomiting, headache, dizziness, or dyspnoea are seen. Severe infusion-related reactions may also occur, usually developing during or within 1 hour following the initial cetuximab infusion. These include rapid onset of airway obstruction, urticaria, hypotension, loss of consciousness and/or angina.

Cetuximab use has been associated with hypomagnasaemia (associated with lethargy and paraesthesia), possibly related to an effect on renal reabsorption, and it is therefore recommended to monitor serum magnesium levels, particularly when used with cisplatin, and replacement therapy given as required.

Dyspnoea has been reported in up to 25% of patients and conjunctivitis may be expected in approximately 5% of patients.

## 8.4 Dose modifications

### 8.4.1 Cisplatin and capecitabine (or 5FU)

#### Haematological

The FBC should be taken and reviewed (up to 3 days) prior to Day 1 of each cycle of chemotherapy.

| Neutrophil / platelet count ( $10^9/L$ ) (day 1)                                                   | Action                                                                                                   |
|----------------------------------------------------------------------------------------------------|----------------------------------------------------------------------------------------------------------|
| ANC $\geq 1$ and/or plts $\geq 75$                                                                 | Full dose drugs                                                                                          |
| ANC 0.5- $<1$ and/or plts 50- $<75$ OR any episode of neutropenic sepsis during the previous cycle | Stop chemotherapy until recovery.
Restart with 25% dose reduction cisplatin and capecitabine (or 5FU) |
| ANC $<0.5$ and/or plts $<50$                                                                       | Stop chemotherapy until recovery.
Restart with 50% dose reduction cisplatin and capecitabine (or 5FU) |

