### **5.2 Assessments during and at end of treatment**

1. A planning CT scan to be carried out during the first cycle of Chemotherapy (weeks 1 to 3)
2. Physical exam to include weight (weeks 1, 4, 7, 8, 9, 10, 11 and 12).
3. Toxicity assessment (baseline, weeks 4, 7, 10, 12 and 13).
4. Full blood count (as a minimum FBC should include haemoglobin, WBC including ANC and platelets) (weeks 1, 4, 7, 8, 9, 10, 11 and 12). Haemoglobin should be maintained above 12g/dL during radiotherapy.
5. Serum renal, liver and bone profile (weeks 1, 4, 7 and 10). Urea, creatinine, sodium, potassium, magnesium, corrected calcium, albumin, bilirubin, AST and/or ALT, ALP and phosphate. (EDTA/24 hour clearance should be performed if renal function deteriorated by more than 25% (Appendix II)).
6. Quality of life QLQ-C30 + oesophageal module (QLQ-OES18) + dermatology life quality index (DLQI)(week 7, 13)
7. State of Health (EQ-5D) (week 7, 13)
8. Healthcare Resource Utilisation Log (week 4, 7, 10, 13)
9. Dysphagia scale

NB: FBC and clinical assessment (CTCAE v3.0 toxicity scores) should be performed on the day of starting each cycle (or within 3 days before) and the results available before starting.

Biochemistry (including creatinine, bilirubin and either AST or ALT) should be done at the same time and the results be available before starting the cycle. This would be considered routine clinical practice.

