#### Nephrotoxicity

Cisplatin produces cumulative nephrotoxicity. If a baseline estimate of renal function using the Cockcroft & Gault formula predicts the GFR to be  $\geq 60\text{mL/min}$  full dose cisplatin should be used. If the estimate is  $<60\text{mL/min}$  an EDTA Creatinine clearance should be performed and the appropriate cisplatin dose used (see table below). In the case of a 25% deterioration in estimated renal function (using the Cockcroft & Gault formula) on pre-treatment blood samples an EDTA Creatinine clearance should be performed and pending this an appropriate dose reduction in cisplatin should be made. The EDTA Creatinine clearance result, when available, takes precedent over estimated GFR for subsequent cisplatin dose calculations.

| GFR (mL/min) Baseline and prior to Day 1 | Action                                                         |
|------------------------------------------|----------------------------------------------------------------|
| $\geq 50\text{mL/min}$                   | Continue full dose                                             |
| 40 - $<50\text{mL/min}$                  | Cisplatin 50% dose
Capecitabine 75% dose                    |
| 30 - $<40\text{mL/min}$                  | Stop cisplatin, use carboplatin AUC 5
Capecitabine 50% dose |
| $< 30\text{mL/min}$                      | Stop cisplatin, use carboplatin AUC 5
Stop capecitabine     |

For a GFR of 50 to  $<60\text{mL/min}$ , a dose reduction of Cisplatin by 50% may be given if local policy.

Consider dose reduction of 5FU in cases of severe renal impairment (i.e.  $\text{GFR} \leq 10\text{mL/min}$ ).

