### 12.2 Outcome measures

#### Stage 1:

The primary outcome measure is treatment failure rate in the research arm. Treatment failure rate will be assessed at 24 weeks (12 weeks after completion of CRT) and is defined as pathologically confirmed (by endoscopic assessment and/or biopsy) residual disease and/or CT scan of thorax and abdomen showing progressive disease according to RECIST criteria.

The secondary outcome measures are: toxicity and feasibility.

- **Toxicity:** will be scored using the NCI CTCAE v3.0 and RTOG acute radiation morbidity scoring criteria (Appendix XII) at baseline, during treatment and at pre-specified time points on follow-up. Serious adverse events will be monitored “real-time” by the Chief Investigator and TMG.
- **Feasibility:** will be measured through the number of protocol dose modifications and delays.

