## APPENDIX II

### Renal Function

Cockcroft & Gault formula

$$\text{GFR for males} = \frac{1.23 \times [140 - \text{age}] \times \text{weight (kg)}}{\text{Serum creatinine } (\mu\text{mol/l})}$$

$$\text{GFR for females} = \frac{1.05 \times [140 - \text{age}] \times \text{weight (kg)}}{\text{Serum creatinine } (\mu\text{mol/l})}$$

- A patient with a Cockcroft & Gault estimate of GFR  $\geq 60$  ml/min using the above formula is eligible for the trial.
- Patients with GFR  $< 60$  ml/min should have confirmation by EDTA clearance, other isotopic method or 24hr creatinine clearance and will be eligible if the GFR  $\geq 40$ .
- After start of treatment, if Cockcroft & Gault estimate falls by 25% from baseline to below 50 ml/min, the EDTA should be performed but an appropriate dose modification made according to protocol pending this result

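### The haematology dosing table in section 8.4.1 gives both full dose and stop to a patient with one adequate and one low count

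*Protocol*

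**What the plan says.** The haematology table in section 8.4.1 of the protocol has three rows, applied to the blood count taken up to 3 days before day 1 of each cycle (counts in 10^9/L).

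- Row 1: "ANC $\geq 1$ and/or plts $\geq 75". The action is "Full dose drugs".
- Row 2: ANC from 0.5 to below 1, and/or platelets from 50 to below 75, "OR any episode of neutropenic sepsis during the previous cycle". Chemotherapy is held until recovery and restarted with both drugs reduced by 25%.
- Row 3: "ANC $<0.5$ and/or plts $<50". Chemotherapy is held until recovery and restarted with both drugs reduced by 50%.

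Section 8.3.1 adds only that counts be monitored and doses modified appropriately. Section 12.2 defines the Stage 1 feasibility outcome, which "will be measured through the number of protocol dose modifications and delays".

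A lesser point concerns repeat measurement of renal clearance, whose trigger is worded in three ways. Section 5.2: "EDTA/24 hour clearance should be performed if renal function deteriorated by more than 25"%, with a cross-reference to Appendix II. Section 8.4.1, Nephrotoxicity: "In the case of a 25% deterioration in estimated renal function", with no floor. Appendix II: "if Cockcroft & Gault estimate falls by 25% from baseline to below 50 ml/min".

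**The concern.** The and/or wording is right in rows 2 and 3, where one low count should be enough to hold treatment. In row 1 it works the other way: one adequate count is enough to permit full dose. A patient with one adequate and one low count therefore meets row 1 and a stop row. Two other overlaps follow. A patient with one count in each low band meets both reduction rows, so the restart dose could be 75% or 50%. A patient whose counts are both adequate on day 1 but who had neutropenic sepsis in the previous cycle meets rows 1 and 2.

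The main stake is safety, because this is the operative dosing rule in both arms of a multi-centre trial. Row 1 alone would allow full-dose treatment with grade 4 neutropenia. The second stake is smaller. If centres read the table differently, the Stage 1 count of dose modifications and delays depends partly on the reader. That count is a secondary measure with no stated threshold, so the effect on the Stage 1 decision is limited.

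**Working it through.** The table states no figure to reproduce. The check is an enumeration.

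**Inputs.** The cut-points come from the section 8.4.1 table: ANC at least 1, 0.5 to <1, and <0.5; platelets at least 75, 50 to <75, and <50. This gives 3 × 3 = 9 combinations. Each row is applied as written, with and/or read as an inclusive or. R1 is full dose, R2 is stop and restart with a 25% reduction, R3 is stop and restart with a 50% reduction.

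**Without sepsis in the previous cycle**

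| | Platelets ≥75 | 50 to <75 | <50 |
|---|---|---|---|
| ANC ≥1 | R1 | R1 + R2 | R1 + R3 |
| ANC 0.5 to <1 | R1 + R2 | R2 | R2 + R3 |
| ANC <0.5 | R1 + R3 | R2 + R3 | R3 |

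- Full dose and stop together: 4 of 9. Two conflict with the 25% row (for example ANC 1.2 with platelets 60, and ANC 0.7 with platelets 90). Two conflict with the 50% row (ANC 1.2 with platelets 40, and ANC 0.3 with platelets 90).
- Both reduction rows: 2 of 9 (ANC 0.7 with platelets 40, and ANC 0.3 with platelets 60).
- One action only: 9 − 4 − 2 = 3 of 9.

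**With sepsis in the previous cycle.** R2 is met in all 9 cells. R1 is still met wherever either count is adequate: 3 + 3 − 1 = 5 cells. So 5 of 9 meet full dose and at least one stop row, and 2 of those 5 meet all three rows.

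**Severity of the examples.** In Appendix XI, neutrophils below 0.5 are grade 4, so ANC 0.3 with platelets 90 is grade 4 neutropenia that satisfies row 1.

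**Is there a precedence rule elsewhere?** None was found. The protocol does state precedence in other places. In the renal part of section 8.4.1 a measured clearance overrides the estimate, and section 11.3 handles serious adverse events at the highest category assigned. The renal dose table uses bands that do not overlap. The haematology table has neither safeguard.

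**Effect of the correction**

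- Row 1 changed to *and* only: the cells with both full dose and stop fall from 4 to 0 without sepsis, but 2 still meet both reduction rows.
- Row 1 also requiring no sepsis: over all 18 combinations (9 with and 9 without sepsis), none meets both full dose and stop, and 2 + 5 = 7 still meet R2 and R3.
- Adding that the most severe row governs: all 18 have one action. Without sepsis, 1 is full dose, 3 are R2 and 5 are R3. With sepsis, 4 are R2 and 5 are R3. The total is 1 + 3 + 5 + 4 + 5 = 18.

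**Renal trigger.** A fall from 100 to 70 mL/min is (100 − 70)/100 = 30%. It calls for re-testing under the wording of sections 5.2 and 8.4.1, but not under Appendix II, because 70 is not below 50. A fall from 80 to 60 is (80 − 60)/80 = 25%, and triggers re-testing under section 8.4.1 only. The section 8.4.1 dose table keeps full dose in both cases (at least 50 mL/min), although the text above it asks for an appropriate cisplatin reduction while the result is awaited.

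**The case against.** The strongest reply is that the table can be read sensibly as a whole. Rows 2 and 3 are specific stop instructions set off by a single low count. If row 1 overrode them, their and/or would have no function, and the sepsis clause would lose most of its purpose in patients whose counts had recovered by day 1. Section 8 places chemotherapy under oncologists in specialist units, who would let the worse count decide. That is very probably what was intended. It bears on how often harm would follow, but it does not supply the missing rule.

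The second reply is frequency. Section 8.3.1 describes myelosuppression as uncommon with these drugs. Table 1 in section 2.3 lists one grade 3 neutropenia among 31 oesophageal patients and one among 7 gastric patients, and no grade 4 neutropenia. Entry requires ANC of at least 1.5 and platelets of at least 100. This stands, and it is why 4 of 9 must be read as cells of the table and not as a share of patients. Table 1 reports only grades 3 and 4, so it says nothing about platelets between 50 and 75, which are grade 2 in Appendix XI.

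Third, where both reduction rows apply, both say to hold treatment, so only the restart dose is open. That is correct.

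Fourth, no effect on overall survival, type I error or power has been shown. Also correct, and none is claimed.

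On the renal trigger, section 5.2 refers the reader to Appendix II, so it is hardly an independent rule. What remains is the floor of 50 mL/min in Appendix II against none in section 8.4.1, which mainly decides whether a test is done.

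**Conclusion.** The concern holds. As written, the table gives contradictory instructions in 4 of 9 count combinations without sepsis and in 5 of 9 with it. It leaves the restart dose open in 2 more of the 9 without sepsis. The count rests on reading and/or as an inclusive or and on there being no precedence rule in the protocol. How many patients would be affected cannot be derived from the document.

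This should be fixed because it is a dosing rule with a safety consequence. Its weight is moderate: the intended reading is easy to guess, low counts are expected to be uncommon, and the effect on the Stage 1 feasibility measure is limited. The renal mismatch is minor, and the conclusion does not depend on it.

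**What to change.** In section 8.4.1:

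- Reword row 1 as *ANC ≥1 and platelets ≥75, with no neutropenic sepsis in the previous cycle*.
- Keep and/or in rows 2 and 3.
- Add under the table: *if more than one row applies, the most severe row governs*.

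Stage 1 dose modifications and delays should then be counted against the corrected table.

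As a secondary tidy-up, use one trigger for repeat measured clearance in section 5.2, section 8.4.1 and Appendix II. State that the cisplatin dose while the result is awaited follows the GFR table in section 8.4.1: full dose at 50 mL/min or above, apart from the existing local-policy option from 50 to below 60.

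The cost is a short protocol clarification sent to all centres. It needs no new data and does not change the sample size or the analysis.
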